### 7.2.1 Baseline characteristics

Baseline demographics and clinical characteristics including ethnicity, age, gender, myopia onset, visual acuity, SER, wearing time of habitual spectacles on all randomised participants will be summarised using descriptive statistics.

### 7.2.2 Treatment effects

The effectiveness of myopic control will be calculated as:

1 – (progression therapy) / (progression control)

Unpaired t-test will be used to compare the changes in primary outcomes between two groups. If statistically significant differences in baseline demographic characteristics between groups are found, these significant covariates will also be adjusted in these primary analyses with Analysis of Covariates. In this case, both the unadjusted and adjusted results will be reported. Multiple regression analysis with the primary outcomes at the final visit will act as the dependent variable and independent variables, alongside with the secondary outcomes, will be employed to identify factors that may associate with myopia control effectiveness.

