### 4.2.2 DIMS lenses

Defocus Incorporated Multiple Segments, DIMS lens is an optical method to control myopia progression (15). It adopts concept of myopic defocus, which a positive-powered lens relative to refractive error of the user is embedded, so the focal plane of the image is cast in front of the retina, which induces a “stop” signal for eye elongation. Myopic defocus has been shown to inhibit myopic eye growth in animal models including in chicks, guinea pigs, tree shrew, and monkeys (16). In DIMS lens, a +3.50D myopic defocus is incorporated in defocus incorporated multiple segments (DIMS) spectacle lenses. DIMS spectacle lenses consist of a central 9-mm optical zone with distant correction which provides a clear distance vision, and it is surrounded by multiple tiny spots of myopic defocus lenses (+3.50D) at periphery. Myopia progression was significantly retarded by about 60% in schoolchildren wearing DIMS spectacle lenses in a 2-year randomized controlled study comparing with no intervention is adopted (8). DIMS spectacle lenses are now commercially available as one of the non-invasive myopic control interventions.

However, none of the currently available intervention completely halts myopia progression and their effectiveness varies between individuals. It is found that the younger the schoolchildren they are, the less effective the myopic control interventions are (12). Therefore, it is crucial to explore treatment strategies that have potential for increased effectiveness and may completely halt myopia progression, thereby avoiding development of high myopia.

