## 6.10 Primary Outcome Measure

The primary outcome measures are changes in cycloplegic refraction in spherical equivalent and axial length over 18 months from baseline, as measured by cycloplegic autorefraction (Shin-Nippon open-field autorefractor) in both eyes and by IOL Master 500 (Carl Zeiss) respectively.

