# 7. Statistical Considerations

## 7.1 Sample Size

In the study regarding low dose atropine for myopia control, mean change in refractive error after one year was 0.64 ± 0.56D (mean ± SD) (10). Our previous randomized clinical trial showed DIMS slowed down myopia progression by approximately 60% (8). The sample size is calculated based on an assumption that, adopting atropine and DIMS together will result in a 60% reduction of mean refractive error change relative to using only atropine, the difference detected between two groups (atropine alone vs. atropine and DIMS) will be 0.384 (0.64 x 60% = 0.384), and the effect size will be 0.685 (0.384/0.56 = 0.685). According to power analysis (G*Power Version 3.1.9.2), 46 subjects are required per group to achieve 90% power with a significance level of 0.05 (two-tailed). Assuming the dropout rate will be 20%, 56 subjects will be required for each group in this proposal. Therefore, 112 subjects (56 subjects × 2 groups) will be required for the entire study.

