## 7.2 Statistical analysis

Statistical analyses will be performed using SPSS. Data of right eyes will be used for analyses. Data from the trial will be entered into an excel spreadsheet and extracted into a statistical program for analysis. Data analyses will be specified *a priori* in a statistical analysis plan (SAP) prepared by the researchers (and agreed upon by all members of the Steering Committee). All statistical tests will be two-tailed and a 5% significance level maintained throughout the analyses.

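### Covariates enter the primary comparison only after a significant baseline demographic test, which gives up precision the collected data could provide and leaves the governing result unnamed when the test is positive.

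*Combined protocol and SAP*

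**What the plan says.** Section 7.2.2, repeated in the Statistical Methods part of Section 1, compares the change in each primary outcome between arms by an unpaired t-test. Adjustment is conditional: "If statistically significant differences in baseline demographic characteristics between groups are found, these significant covariates will also be adjusted in these primary analyses". If that happens, "both the unadjusted and adjusted results will be reported". Neither section says which of the two carries the conclusion.

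Section 1 names the demographics as age and sex. It also plans baseline tests of the primary and secondary outcomes, but a significant difference in those does not trigger adjustment. Baseline spherical equivalent refraction (SER) and axial length (AL) therefore cannot enter the primary comparison by this route, although both are measured at baseline (Sections 6.9 and 6.12).

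On age, Section 4.2.2 says that "the younger the schoolchildren they are, the less effective the myopic control interventions are".

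Section 7.2 says that analyses will be set out in advance in a statistical analysis plan agreed by the Steering Committee. Section 7.2.4 makes the main analysis intention-to-treat with multiple imputation, and complete-case analysis a sensitivity analysis.

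**The concern.** After randomisation, a baseline difference between arms is a chance event. Its p-value measures how unusual the chance was, not whether the variable is related to progression. The choice of covariates should rest on that relation and can be made before any data are seen.

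The protocol's own background ties age to treatment response, and both arms receive atropine across ages 7 to 12. Yet age is left out unless it happens to differ at the 5% level.

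Two things are at stake. One is precision: if age and the baseline value predict 18-month change, fixed adjustment narrows the confidence interval at no cost in recruitment. The other is prespecification: the form of the primary model depends on the data, and when the trigger fires two estimates and two p-values exist for one question with no stated order.

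**Working it through.** **Inputs from Section 7.1.** Control-arm change 0.64 D, SD 0.56 D, assumed reduction 60%, two-sided alpha 0.05, power 90%, 46 evaluable per arm, 20% dropout, 56 recruited per arm. These concern refraction only. The documents give no corresponding figures for axial length, so the power figures below are for SER.

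**Input not in the documents.** r, the correlation between the covariates and 18-month change within arm. It is assumed, and shown from 0 to 0.5.

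**1. The plan's own figure.** Difference 0.60 × 0.64 = 0.384 D; effect size d = 0.384/0.56 = 0.686. Power comes from the noncentral t distribution with 2n − 2 degrees of freedom and noncentrality d√(n/2). At n = 45 it is 89.6% and at n = 46 it is 90.2%. The stated 46 reproduces, and it is the right number for an unadjusted t-test.

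**2. Completers.** 56 × 0.80 = 44.8. Taking 44, the noncentrality is 0.6857 × √22 = 3.216 and power is 88.9%.

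**3. Fixed ANCOVA at 44 per arm.** Residual SD = 0.56√(1 − r²), so the effect size becomes 0.6857/√(1 − r²).

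| r (assumed) | Residual SD (D) | Effect size | Power |
| --- | --- | --- | --- |
| 0 (t-test) | 0.560 | 0.686 | 88.9% |
| 0.1 | 0.557 | 0.689 | 89.2% |
| 0.2 | 0.549 | 0.700 | 90.1% |
| 0.3 | 0.534 | 0.719 | 91.5% |
| 0.4 | 0.513 | 0.748 | 93.4% |
| 0.5 | 0.485 | 0.792 | 95.7% |

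The gain is 0.3 points at r = 0.1 and 1.2 points at r = 0.2, and becomes material from about r = 0.3.

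**4. How often the trigger fires.** With two independent 5% tests (age, sex), the chance that at least one is significant is 1 − 0.95² = 9.75%.

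**5. What the conditional rule recovers.** Simulation with 20,000 trials, 45 per arm, r = 0.4:

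| Analysis | Power | Rejection under the null |
| --- | --- | --- |
| Unadjusted t-test | 89.7% | 4.8% |
| Conditional rule (adjusted result used when triggered) | 90.0% | 4.4% |
| Fixed ANCOVA | 93.7% | 4.7% |

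The Monte Carlo standard error is about √(0.9 × 0.1/20,000) = 0.2 points for power. The conditional rule cannot be told apart from the t-test at this precision, while the gain from fixed ANCOVA is 93.7 − 89.7 = 4.0 points.

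**6. When the trigger fires.** A second simulation (46 per arm, age and sex tested, age explaining 10% to 30% of the variance, no treatment effect) put the adjusted and unadjusted results on opposite sides of p = 0.05 in about 5% to 12% of triggered trials. Over all trials that is 0.0975 × 0.05 to 0.0975 × 0.12, or about 0.5% to 1.2%. Claiming success if either result is significant gives an overall type I error of about 5.1% to 5.6%.

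**The case against.** **The planned analysis is valid.** This stands. Overall type I error is 4.8% for the t-test and 4.4% for the conditional rule in the simulation above, and the sample size was calculated for the t-test. A reader might infer inflated error from the case of an age imbalance just short of the trigger: at 1.9 standard errors and r = 0.4, the t-test's conditional error is 9.7%. That is close to the worst untriggered case. Imbalances between 1.9 and 1.96 standard errors occur in about 0.7% of trials. With no imbalance the conditional error is 3.2%, and averaged over all untriggered trials it is about 4.6%.

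**Competing results are rare.** This also stands. A reader might infer that the plan always yields two primary results. In about 90% of trials the t-test is the only one, and even when both exist they usually agree on significance.

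**The gain rests on assumed correlations.** Correct. Section 4.2.2 gives a direction for age but no strength, and the documents say nothing about how well baseline SER or AL predicts change. If the covariates are weak, the gain is negligible. If age alters the added effect of the DIMS lens, a main-effect covariate does not address that.

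**The power figures are for completers.** Correct. The planned main analysis imputes missing outcomes for all randomised children, so 44 and 45 per arm only approximate it.

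**The detail may be settled in the separate analysis plan.** Possibly, but Section 7.2.2 already states the conditional rule, and nothing in the supplied text replaces it or ranks the results.

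**Right eyes.** A reader might also object that refraction is measured "as measured by cycloplegic autorefraction (Shin-Nippon open-field autorefractor) in both eyes" while "Data of right eyes will be used for analyses". A one-eye analysis chosen in advance is valid and avoids handling correlation between eyes, so the documents support no criticism there.

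**Conclusion.** The concern holds as one of efficiency and prespecification. The trigger selects covariates on a criterion unrelated to their value, excludes baseline SER and AL altogether, and when it fires by chance (about 10% of trials, taking age and sex as two independent 5% tests) leaves two results without an order. The documents do not support a claim that the primary test is invalid or that the sample size is wrong.

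The size of the loss for refraction depends on r: from 0.3 points of power at r = 0.1 to 95.7 − 88.9 = 6.8 points at r = 0.5, with 44 completers per arm. The direction holds for any covariate that truly predicts change. The textual facts are certain; the size is conditional on the assumed r and on the complete-case approximation.

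**What to change.** For each primary outcome, name one primary analysis: ANCOVA of 18-month change on arm, with age and the baseline value of that outcome (SER for refraction, AL for axial length) as fixed covariates whatever the baseline comparison shows. Delete the significance trigger from Sections 1 and 7.2.2; baseline characteristics can be described by arm without tests. Report the unadjusted t-test as a sensitivity analysis, and state that the ANCOVA governs. The right-eye analysis can stay as planned.

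The cost is a change of wording, settled before unblinding, and two degrees of freedom per model. Age, SER and AL are already collected at baseline, and neither the recruitment target nor any visit changes.

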### 7.2.3 Tolerability

Treatment will be discontinued if any treatment-related adverse event arises, such as atropine allergy, constant visual disturbance (e.g. ghosting, diplopia, glare etc.). The number of participants discontinuing treatment prematurely for any reason will be summarised by treatment group and by reasons for discontinuation. The incidence of all serious adverse events will be summarised by treatment group.

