## 6.7 Withdrawal Criteria

Participants (or parents / guardians for participants <18 years of age) are free to withdraw from participation in the study at any time upon request. No further data will be collected on participants who withdraw themselves from this study. If significant intolerance to study treatment is suspected at any time after randomization, participants may be requested to withdraw from the study at any time.

An investigator may discontinue or withdraw a participant from the study due to the following reasons:

- Significant study intervention noncompliance: unable to contact via three phone calls, more than three attempts to arrange missed follow-up appointments, wearing the spectacles less than five days a week and / or weekly average less than five hours/day.
- If any clinical adverse event or situation occurs (e.g. allergies to eye drops, reduction of visual function such as diplopia, reduction of BCVA; subject to clinicians’ judgement) such that continued participation in the study would not be in the best interest of the participant.
- If the participant meets an exclusion criterion (either newly developed or not previously recognized) that precludes further study participation.

Should participants require discontinuation of study treatment for any reason, or if they select to cease taking treatment, follow-up visits and data collection will not be continued as scheduled. The reason of discontinuation or withdrawal of participant from the study will be recorded on the Discontinuation / Withdrawal Case Report Form (CRF W) in Research Electronic Data Capture (REDCap). The use of REDCap can help reduce human errors in the randomization process, to assist data collection, and to provide a real-time dashboard for monitoring the project progress. Participants who sign the informed consent form, and are randomized but do not receive the study intervention may be replaced. If there are participants who signed the informed consent form, are randomized and received the study interventions but discontinue or withdraw within the first two weeks due to inability to meet inclusion criteria (e.g. unable to tolerate spectacles or eyedrops), and it is still within the recruitment period, then randomization of these participants will be discarded and replaced with a participant from the next allocation. All spectacles and eye drop (used or unused) will be returned to the investigator on withdrawal or discontinuation from the study.

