Information to be collected includes event description, time of onset, clinician’s assessment of severity, relationship to study product (assessed only by those with the training and authority to make a diagnosis), and time of resolution or stabilization of the event. All AEs occurring while on study must be documented appropriately regardless of relationship. All AEs will be followed to adequate resolution. An appointment will be arranged for four to six weeks following AE resolution to check for any recurrence or changes as a result of the AE. Changes in the severity of an AE will be documented to allow an assessment of the duration of the event at each level of severity to be performed. AEs characterized as intermittent require documentation of onset and duration of each episode. These will be followed-up and assessed by medically fit clinician. It will be left to the judgement of the Steering Group to decide whether or not an AE is of sufficient severity to require discontinuing the participant from the study. A participant may also voluntarily withdraw from participating in the study due to what he or she perceives as an intolerable AE. If either of these occurs, the participant must undergo follow-up visits for trial assessment and be given appropriate care under medical supervision until symptoms cease, or the condition becomes stable.

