### 9.2.2 Significant Adverse Events

Events that are usually symptomatic and warrant discontinuation (temporary or permanent) of the test article (excluding Serious Adverse Events).

Diagnoses and conditions that are considered Ocular Significant Adverse Events include, but not limited to the following:

- Any Temporary Loss of > two Lines of BCVA.
- Other grade three or higher corneal findings, such as abrasions or oedema.
- Non-contact lens related corneal events - e.g. Epidemic Keratoconjunctivitis (EKC).
- Asymptomatic Corneal Scar.
- Intermittent Spiking of Intraocular Pressure.
- Any corneal event which necessitates temporary eyedrop discontinuation > two weeks.

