### 9.2.3 Non-Significant Adverse Events

Conditions that are usually asymptomatic and usually do not warrant discontinuation (temporary or permanent) of the test article. However, the investigator may choose to treat as a precautionary measure.

Diagnoses and conditions that are considered Ocular Non-Significant Adverse Events include, but not limited to the following:

- Conjunctivitis: Bacterial, Viral, Allergic
- Blepharitis
- Meibomianitis
- Contact Dermatitis
- Localized Allergic Reactions
- Any corneal event not explicitly defined as serious or significant adverse event, which necessitates temporary eye drops discontinuation < two weeks.

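### Section 7.2.3 stops treatment for any related adverse event, against section 9.2.3, and section 6.7 then ends scheduled measurement, so some 18-month outcomes would be imputed rather than observed

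*Combined protocol and SAP*

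**What the plan says.** **When treatment stops.** Section 7.2.3: "Treatment will be discontinued if any treatment-related adverse event arises, such as atropine allergy, constant visual disturbance". It sets no severity threshold and does not mention temporary pauses. Section 9.2.3 describes non-significant events as "Conditions that are usually asymptomatic and usually do not warrant discontinuation (temporary or permanent) of the test article". Its list includes "Localized Allergic Reactions", contact dermatitis and allergic conjunctivitis. Section 9.2.2 ties stopping to the significant class: "Events that are usually symptomatic and warrant discontinuation (temporary or permanent) of the test article".

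**Who decides.** Section 6.7 is permissive: "An investigator may discontinue or withdraw a participant from the study due to the following reasons". Its adverse-event reason is left to the clinician's judgement. Section 9.1.2 says it is "left to the judgement of the Steering Group to decide whether or not an AE is of sufficient severity" for the child to leave the study.

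**What happens afterwards.** Section 6.7 says that when treatment is stopped, whatever the reason, "follow-up visits and data collection will not be continued as scheduled". Section 9.1.2 says that after an adverse event leads to discontinuation from the study, or to voluntary withdrawal, "the participant must undergo follow-up visits for trial assessment and be given appropriate care under medical supervision until symptoms cease" or the condition is stable.

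**How the gap is filled.** Section 7.2.4 declares all analyses intention-to-treat. Missing outcomes are multiply imputed (10 sets) under missing at random, with complete-case and per-protocol analyses as sensitivity analyses.

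**The concern.** Two members of staff, each following the protocol, could handle the same mild drop reaction in opposite ways: one stops treatment under 7.2.3, the other continues it under 9.2.3. No section says which rule takes precedence.

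The choice affects more than treatment. Under 6.7 a stop also ends scheduled measurement, so a mandatory stop for a mild event becomes a missing primary outcome. An intention-to-treat comparison is best served by measuring every randomised child at 18 months, on treatment or not. Here the plan itself would create missing values that could have been observed, and then rely on an untestable assumption to fill them.

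**Working it through.** **Step 1. Apply each rule to one case:** a mild localised allergic reaction that a clinician attributes to the drops.

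- Section 7.2.3: related, so treatment stops. Atropine allergy is one of its named examples.
- Section 9.2.3: on the non-significant list, so usually no stop, temporary or permanent.
- Section 9.2.2: not in the significant class, so its stopping provision does not apply.
- Sections 6.7 and 9.1.2: withdrawal from the study is a matter of judgement.

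The defaults in 7.2.3 and 9.2.3 are opposite.

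**Step 2. Find how wide the overlap is.** Section 9.1.2 counts an event as related only if its timing fits and no other cause is reasonable. Bacterial or viral conjunctivitis, blepharitis and meibomianitis would seldom qualify, so 7.2.3 would rarely reach them. What remains is mainly allergic and contact reactions to the drops.

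**Step 3. Follow the stopped child's data.**

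- Section 6.7 ends scheduled visits and data collection.
- Section 9.1.2 requires visits only until the event resolves or stabilises. For a mild reaction that may be well before month 18.
- No section secures the 18-month refraction and axial length.
- Section 7.2.4 then imputes both under missing at random.

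**Step 4. Gauge the scale.** Inputs from section 7.1: difference 0.384 D, SD 0.56 D, effect size 0.685, two-sided alpha 0.05, power 90%, 46 per group, 20% dropout, 56 enrolled per group.

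*Plan's own figure.* The two-sample t-test at d = 0.685 needs 45.77 per group, rounded up to 46, with power 0.901. The enrolled figure follows from 46 × 1.2 = 55.2, rounded up to 56. Dividing instead, 46 / 0.8 = 57.5, gives 58. The small difference is not the issue here.

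*Extra loss.* Let f be the share of the children left after 20% dropout who are also lost through stops under 7.2.3 and 6.7. The documents give no event rate, so f is an assumption.

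Observed per arm: n = 56 × 0.8 × (1 − f). Power comes from the noncentral t distribution with 2n − 2 degrees of freedom and noncentrality 0.685 × √(n/2).

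| f | n per arm | noncentrality | power |
| --- | --- | --- | --- |
| 0 | 44.8 | 3.24 | 0.894 |
| 5% | 42.6 | 3.16 | 0.878 |
| 10% | 40.3 | 3.08 | 0.859 |
| 20% | 35.8 | 2.90 | 0.816 |

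These are complete-case values. The primary analysis uses multiple imputation, so they show scale only.

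**The case against.** **The wording leaves room.** The examples in 7.2.3 suggest that only troublesome events were meant, and 9.2.3 says *usually*. This narrows the conflict, as Step 2 shows. It does not remove it: the operative word in 7.2.3 is *any*, and atropine allergy is named.

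**Section 9.1.2 already requires trial follow-up.** Its end point could be read as limiting only the medical care and not the visits. On that reading 9.1.2 contradicts 6.7 outright. On the other reading the visits stop when the event settles. Either way the text needs reconciling.

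**Harmonising 7.2.3 with 9.2.3 does not by itself rescue the outcome data.** This is correct. Section 6.7 ends measurement after any stop, so it needs its own change.

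**Stronger readings that the documents do not support.**

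- A reader might infer that the conflict produces unequal stopping between arms. Both arms receive the same 0.01% atropine twice daily, and nothing in the documents suggests that drop reactions differ by arm. Glare and ghosting could differ with the lens, but they are symptoms and are not on the 9.2.3 list. Constant disturbance sits closer to 9.2.2, which agrees with 7.2.3 on stopping.
- A reader might infer that the by-arm discontinuation table would be uninterpretable. Section 7.2.3 tabulates stops by reason, and section 9.1.2 records severity, relatedness and action taken for each event.
- A reader might see an error in the lack of a planned by-arm table of non-serious events. That is unspecified detail: section 7.2 promises a separate SAP, and the Overview says CONSORT will guide reporting.

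**Conclusion.** The point stands as minor. The documents give opposite defaults for mild allergic or contact reactions attributed to the drops. Section 6.7 then turns a stop into a missing 18-month outcome that 9.1.2 does not secure. These are stated rules that give a worse result if followed, not merely missing detail.

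The size is modest and rests on assumed losses. Complete-case power goes from 89% to 88%, 86% or 82% with 5%, 10% or 20% extra loss. The plan does not say whether its 20% dropout already includes adverse-event stops; if it does, there is no extra loss. The imputed analysis keeps these children in the comparison, so the cost is outcomes assumed rather than measured. Nothing here indicates that the primary result would be reversed.

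**What to change.** 1. **Section 7.2.3, first sentence.** Replace it with a rule that matches section 9.2: treatment is stopped, temporarily or permanently, for serious or significant events; non-significant events bring no automatic stop; the clinician may stop treatment at any time for safety.
2. **Section 6.7.** State that a child who stops treatment because of an adverse event stays in the remaining 6-, 12- and 18-month visits for cycloplegic autorefraction and axial length, unless the family declines. Align section 9.1.2, so that care for the event may end when it settles but outcome visits continue to month 18.

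**Cost.** A short amendment with approval by both review boards (section 13.2). At most three visits per affected child are kept, all already in the section 6.12 schedule. No new test or analysis is needed. Fewer automatic stops means more reliance on clinical judgement, so the freedom to stop for safety must be explicit.
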